## **2. Overview**

### **2-1. Study Design**

Multicenter, randomized, crossover, double-blind.

### **2-2. Objective**

The objective of this study is to evaluate the effects of consuming boysenberry juice for four weeks on diet-induced thermogenesis and associated energy expenditure.

### **2-3. Subjects**

Healthy adults.

### **2-4. Intervention**

Based on the eligibility assessment results at the time of registration, the following interventions will be performed: Participants will consume either 100 mL of boysenberry juice or 100 mL of placebo beverage daily during the four-week study period.

### **2-5. Outcomes**

- 1) Changes in postprandial thermogenesis after four weeks of intake.
- 2) Changes in energy expenditure after four weeks of intake.
- 3) Changes in body composition after four weeks of intake.
- 4) Changes in oxygen consumption, carbohydrate oxidation, fat oxidation, and respiratory quotient after four weeks of intake.
- 5) Changes in subjective indicators after four weeks of intake.

### **2-6. Target Sample Size and Study Period**

Target sample size: 36 participants.

Study period: From the date of approval to March 31, 2024.

### **3. Background**

Brown adipose tissue (BAT) has been identified as an important tissue for metabolic regulation throughout the body, in addition to its role as a thermogenic organ. The activity of brown adipose tissue decreases with age, and it has been reported to be significantly inversely correlated with BMI and body fat, representing a novel therapeutic target for age-related diseases such as obesity and metabolic disorders. BAT promotes energy expenditure through non-shivering thermogenesis in cold environments, and it is also suggested to contribute to energy expenditure through daily thermogenesis. Diet-induced thermogenesis (DIT), the phenomenon of heat production following food intake, is a well-known physiological process, and BAT has been reported to contribute to DIT and promote energy expenditure, indicating its potential importance in the prevention of various diseases.

Polyphenolic compounds found in foods have been reported to possess various health benefits. Some polyphenolic compounds have been shown to activate BAT, which may be utilized for therapeutic and preventive strategies targeting BAT function. Boysenberry, a berry fruit rich in polyphenols, contains anthocyanin compounds in boysenberry juice that have been found to potentially improve and protect vascular endothelial function, thereby enhancing cardiovascular function. Additionally, we have obtained data suggesting that the intake of boysenberry polyphenols may suppress or improve the decline in BAT function in mice. Additionally, preliminary investigations conducted on humans have shown that the intake of boysenberry juice for four weeks increases thermogenesis in the supraclavicular region, considered to be a site of BAT, during cold exposure, suggesting an improvement in BAT function (data not yet published, UMIN000043476). On the other hand, the effects of polyphenol intake on daily energy expenditure, such as DIT, are not well understood, and further elucidation through intervention studies involving humans is needed.

### **4. Objectives**

Based on previous research findings, we hypothesize that the intake of boysenberry juice may increase daily energy expenditure, specifically DIT, and postprandial energy expenditure through the improvement of BAT function. This study aims to investigate the effects of the consumption of boysenberry and placebo beverages on DIT and associated postprandial energy expenditure in healthy adults through a crossover trial, thereby elucidating the impact of polyphenols.

### **5. Overview of Test Foods**

### 1) Boysenberry Juice

Nutritional components per 100 mL:

Energy: 32 kcal

Carbohydrates: 7.3 g

Protein: 0.4 g

Fat: 0.1 g

Sodium: 0 mg

Total Polyphenols: 294 mg

Anthocyanins: 79 mg

### 2) Placebo Beverage

The placebo beverage was designed to match the carbohydrate and organic acid content of the boysenberry juice in 1), and the appearance and flavor were adjusted using coloring agents and flavoring agents to be similar to that of 1).

### Safety Information

Boysenberry juice is a commercially available beverage with no reported adverse events to date, indicating that there are no safety concerns.

## 6. Subjects

### 6-1. Study Participants

Healthy adult males and females.

### 6-2. Recruitment Method

Participants will be broadly recruited through the posting of posters and distribution of leaflets at various locations such as companies, universities, sports clubs, and health clubs, allowing for voluntary participation.

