## **6-4. Exclusion Criteria**

1. Individuals with any diseases who are undergoing drug treatment.
2. Individuals suffering from severe diseases or allergic conditions.
3. Individuals who regularly consume supplements or health foods during the study period.
4. Individuals who excessively consume foods containing polyphenols during the study period.
5. Individuals who are expected to undergo significant changes in exercise habits, job, or academic lifestyle during the study period.
6. Pregnant or nursing women.
7. Individuals deemed unsuitable by the principal investigator.

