## **15. Target Sample Size and Rationale**

36 participants.

[Rationale for Setting Criteria]

In a preliminary open-label, before-and-after comparison study involving 10 participants, the effects of the test food on brown adipose tissue were evaluated. The increase in skin temperature in the supraclavicular area during cold exposure before and after the consumption of the test food was used as an indicator to analyze the function of brown adipose tissue. Based on this data, the sample size was calculated with a power of 95%

and a significance level of 0.05, resulting in a calculated sample size of 22 participants. However, since this study uses different indicators than the preliminary trial, previous literature was referenced, and significant differences were observed in a crossover trial involving 36 participants. Therefore, it was assumed that a sample size of more than 22 and less than 36 participants would be necessary to obtain significant differences in this study, leading to the establishment of the sample size of 36.

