#### **18.2. Conflict of Interest**

The principal investigator and co-investigators include members affiliated with Bourbon Corporation, the funding provider, as well as individuals in the collaborative research course at Juntendo University funded by Bourbon. However, measurements will be carried out by investigators from Niigata University who do not have a direct conflict of interest with Bourbon to ensure that Bourbon does not have any involvement in these

aspects. Furthermore, blinding will be maintained until all data analyses are completed to prevent any potential bias that could favor Bourbon Corporation. All researchers will manage conflicts of interest appropriately in accordance with their respective organizations' conflict of interest management policies and will disclose such conflicts upon request when presenting research results at conferences or publishing in medical journals.

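### The eligibility criteria do not exclude people who have already taken the juice openly, or the funder's staff, so the participant blind is at avoidable risk

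*Protocol*

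**What the plan says.** Recruitment (Section 6-2) is broad, by "posting of posters and distribution of leaflets at various locations such as companies, universities, sports clubs, and health clubs". No source is ruled out and none is tied to the funder.

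The protocol itself shows that some people already know the product. Section 15 begins its rationale with "In a preliminary open-label, before-and-after comparison study involving 10 participants, the effects of the test food on brown adipose tissue were evaluated". Section 3 reports that "preliminary investigations conducted on humans have shown that the intake of boysenberry juice for four weeks increases thermogenesis in the supraclavicular region". Under Safety Information in Section 5, "Boysenberry juice is a commercially available beverage with no reported adverse events to date".

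The inclusion criteria (6-3) cover age, health, BMI and consent. Of the exclusion criteria (6-4), three could touch people who know the juice: number 3 (regular supplements or health foods while the study runs), number 4 (excessive polyphenol foods while the study runs) and number 7, "Individuals deemed unsuitable by the principal investigator". The background items in 9-2 1) include polyphenol and supplement use. They do not include employer, earlier participation in the pilot, or familiarity with boysenberry juice.

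On conflict of interest, Section 18.2 states that "The principal investigator and co-investigators include members affiliated with Bourbon Corporation, the funding provider", and that people from the funder-financed course at one of the universities also take part as investigators. It gives two safeguards: measurement by investigators at the other university, and that "blinding will be maintained until all data analyses are completed to prevent any potential bias that could favor Bourbon Corporation".

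**The concern.** The participant side of the blind has two supports: allocation is not disclosed (9-3), and the placebo is made to resemble the juice in look and flavour (Section 5). The second support is weakest in someone who remembers the real product. In a parallel trial such a person could judge only the one beverage received. In this crossover they take both, so recognising either one reveals the sequence.

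Two groups stand out. Pilot participants took the test food knowing what it was. The funder's employees and members of its financed course may know the product and may have an interest in the result. Section 18.2 names blinding as its protection against bias towards the funder. Its other safeguard acts on those who measure, not on a participant who recognises the drink.

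What is at stake is mainly the subjective indicators. These are a secondary outcome (10-2) that participants rate themselves on a VAS before the test meal and after the last post-meal measurement (9-2 6)). A weaker route is behaviour outside the laboratory: daily intake, the dietary record, and exercise on the day before testing. If prior exposure is never recorded, no later analysis can separate those who had it from those who did not.

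**Working it through.** **Step 1. Set each group against the criteria.**

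| Group | Named in 6-3 or 6-4? | Other rule that may apply | Identified by 9-2 1)? |
|---|---|---|---|
| Open-label pilot participants (10, Section 15) | No | Criterion 7 only | No |
| Funder's employees, members of its financed course | No | Criterion 7 only | No |
| Current regular drinkers of the juice | No | Criteria 3, 4 or 7, depending on interpretation | In part, through polyphenol intake |
| Former drinkers | No | Criterion 7 only | No |

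For current drinkers, 100 mL of the juice carries 294 mg of polyphenols (Section 5), so criterion 4 could apply. It has no threshold, however, and criterion 3 does not define health foods. Both refer to the study period and not to past use.

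**Step 2. Upper bound on pilot participants.** The target is 36 (8-3) and the pilot had 10 people, so at most 10/36 = 27.8% of places. This needs all ten to return and qualify. It is a ceiling, not a forecast.

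**Step 3. How much a few such participants could matter (assumed inputs).** Section 14 names the paired t-test among its methods. Suppose there is no true effect, and k of 36 participants recognise the juice and each shifts their juice-minus-placebo difference by b standard deviations of that difference. The mean shift is δ = b × k/36, and the noncentrality of the t statistic is δ × √36 = 6δ. The SD is taken as unchanged. Neither k nor b is in the protocol.

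| k | b (SD) | δ | 6δ | Two-sided type I error at nominal 0.05 |
|---|---|---|---|---|
| 1 | 0.25 | 0.007 | 0.04 | 0.050 |
| 3 | 0.5 | 0.042 | 0.25 | 0.057 |
| 5 | 0.5 | 0.069 | 0.42 | 0.069 |
| 10 | 0.5 | 0.139 | 0.83 | 0.128 |
| 10 | 1.0 | 0.278 | 1.67 | 0.37 |

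The effect is negligible for one person and small for three. It becomes material only if many exposed people enrol and the outcome responds to expectation.

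**Step 4. Would the exclusion harm the sample size?** Section 15 calculates 22 participants at 95% power and a significance level of 0.05. This figure cannot be reproduced, because the pilot's mean change and SD are not given. Solving backwards for a two-sided paired t-test, 22 participants correspond to a standardised effect of about 0.81 (about 0.73 one-sided; sidedness is not stated). In the extreme case that all ten pilot participants would have enrolled and none were replaced, 36 − 10 = 26 remain, still above 22. At the back-solved effect of 0.81, power is 97.7% with 26 and 99.7% with 36. That effect belongs to the pilot's cold-exposure skin temperature and not to this trial's primary outcome. The step therefore shows only that the exclusion does not break the protocol's own rationale.

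**The case against.** The strongest reply is that nothing here is shown to go wrong. The recruitment text mentions companies in general, not the funder. No section says that pilot participants will be invited again, or how widely the juice is drunk. The placebo was matched on carbohydrate and organic acid and adjusted in look and flavour, so knowing the juice does not amount to telling the two apart. If the match were poor, people new to the juice might notice too, and the proposed exclusion would not test for that. The primary outcome (10-1) concerns energy expenditure and thermogenesis, measured by respiratory gas analysis and thermography after a laboratory rest at a fixed temperature, with dinner and test meal both specified. Section 18.2 also separates measurement from the funder.

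Most of this stands, and it rules out several stronger readings that a reader might infer:

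- That all these people are eligible. Criteria 3 and 4 may already remove current regular drinkers, and criterion 7 could remove anyone.
- That the blind will fail. The documents show a risk and no instance.
- That the bias must favour the juice. The protocol does not define the VAS items, and outside the funder's circle nothing suggests an interest in the result.
- That criterion 7 lies in the funder's hands. Section 18.2 places affiliated members among the principal investigator and co-investigators as a group; it does not say which of them hold the affiliation.

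The objection leaves the gap itself in place. Two clearly identifiable groups are named by no criterion, screening as listed would not find them, and a discretionary rule works only if someone thinks to ask. Eligibility belongs in the protocol, so this is not a matter left to a separate analysis plan.

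**Conclusion.** The point holds as a cheap improvement to the design, not as an error or contradiction in the protocol. Pilot participants, the funder's employees and members of its financed course are not excluded by any specific criterion and would not be identified at screening. Current regular drinkers are partly covered and former drinkers are not. With a crossover, and with Section 18.2 relying on the blind, this is an avoidable risk to participant blinding. It bears mainly on the self-rated VAS and much less on the instrument-measured primary outcome.

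The size cannot be fixed from the documents, because the number of such participants is unknown. The ceiling of 27.8% and the type I error range of 0.050 to 0.37 are illustrations that rest on assumed numbers of participants and assumed shifts. They should not be read as estimates of what will happen.

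**What to change.** Add one exclusion criterion to 6-4: people who took part in the preliminary boysenberry study, employees of the funder, and members of the funder-financed university course. Add one short question to the background items in 9-2 1) covering these points and any previous or regular use of boysenberry juice, so that regular drinkers can be excluded or examined in a sensitivity analysis.

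The cost is one criterion, one screening question and a slightly smaller recruitment pool. The change does not verify that the placebo is indistinguishable from the juice; that is a separate matter.

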### 6-3. Inclusion Criteria

1. Males and females aged 20 years or older at the time of consent.
2. Individuals who are healthy and do not have any chronic diseases.
3. Individuals with a BMI of 18.5 or higher and less than 25.0.
4. Individuals who have provided written informed consent to participate in the study.

## Rationale for Setting Criteria

1. To target capable and healthy adults for informed consent.
2. To ensure evaluation in a population similar to that encountered in routine clinical practice, no upper age limit is set.
3. The criteria have been established in accordance with ethical guidelines.

## **6-4. Exclusion Criteria**

1. Individuals with any diseases who are undergoing drug treatment.
2. Individuals suffering from severe diseases or allergic conditions.
3. Individuals who regularly consume supplements or health foods during the study period.
4. Individuals who excessively consume foods containing polyphenols during the study period.
5. Individuals who are expected to undergo significant changes in exercise habits, job, or academic lifestyle during the study period.
6. Pregnant or nursing women.
7. Individuals deemed unsuitable by the principal investigator.

## Rationale for Setting Criteria

1. To target healthy adults.
2. Because the effective component of the test food is considered to be polyphenols.
3. Because lifestyle factors such as exercise habits and diet may influence the study outcomes.

## **7. Informed Consent**

In conducting this study, informed consent will be obtained in accordance with the "Ethical Guidelines for Life Science and Medical Research Involving Human Subjects."

### **7-1. Procedures for Obtaining Informed Consent**

A consent explanation document approved by the Ethics Committee for Research Involving Human Subjects at the Medical School will be provided to the research participants (including their legal representatives, if necessary). Adequate explanations will be given both in writing and orally, and written informed consent will be obtained based on the participants' free will. If any information arises that may affect the

participants' consent or if there are changes to the research protocol that may influence the participants' consent, the participants will be promptly informed, and their willingness to continue participation in the study will be confirmed beforehand. Any revisions to the consent explanation document will also be made with prior approval from the Ethics Committee, and re-consent from the participants will be obtained.

The consent explanation document will include the following information:

1. The title of the research and a statement confirming that permission has been obtained from the head of the research institution to conduct the study.
2. The name of the research institution and the name of the principal investigator (including the names of the collaborating research institutions and their principal investigators if the research is conducted in collaboration with other institutions).
3. Purpose and Significance of the Research
4. Research Methods (including the purpose of utilizing samples and information obtained from research participants) and Duration
5. Rationale for Selecting Research Participants
6. Burden on Participants and Anticipated Risks and Benefits
7. Statement that Consent to Participate or Continue in the Research Can Be Withdrawn at Any Time (including information on the circumstances and reasons if such withdrawal would make it difficult to implement measures based on the withdrawal)
8. Assurance that Participants Will Not Be Treated Unfavorably for Refusing or Withdrawing Consent to Participate or Continue in the Research
9. Method of Information Disclosure Regarding the Research
10. Statement that Research Plan and Methodology Materials Can Be Obtained or Accessed at the Request of Research Participants, Provided that It Does Not Hinder the Protection of Personal Information of Other Research Participants and the Preservation of the Study's Originality, along with Information on How to Obtain or Access This Material
11. Handling of Personal Information (including methods of anonymization, and a statement regarding the creation of anonymized or non-identifiable information)
12. Methods for the Storage and Disposal of Samples and Information
13. Source of Funding and Status of Conflicts of Interest Related to the Research Institution and Individual Researchers
14. Handling of Results Obtained from the Research
15. System and Contact Points for Research Participants and Their Associates to Consult

Regarding the Research (including genetic counseling)

16. Disclosure of Any Economic Burden or Compensation to Research Participants, Including the Details and Nature of Such Compensation

## **7-2. If Information is Obtained that May Affect Participation in the Research**

If the research physician obtains any information during the study that may influence a participant's decision to continue their involvement in the study, they will immediately explain that information to the participant and confirm their willingness to continue participation. At the same time, the consent explanation document will be revised, and approval will be sought from the Ethics Committee to obtain written consent from the participant for continued participation in the study.

## **8. Research Methods**

### **8-1. Study Design**

Multicenter, randomized, crossover, double-blind.

### **8-2. Outline of the Study**

The researcher will obtain consent from the participants and confirm their eligibility before commencing the trial. The duration of participants' involvement in the study will be as follows:

1. Eligibility assessment and consent form acquisition.
2. Consumption of the test food for four weeks, with testing conducted in the fourth week of consumption.
3. Washout period of four weeks.
4. Change of test food, followed by the consumption of the new test food for four weeks, with testing conducted in the fourth week of consumption.
5. Study conclusion.

A schematic outline is provided below.

[figure not shown]

### 8-3. Target Sample Size and Study Period

Target sample size: 36 participants (6 participants from Juntendo University, 30 participants from Niigata University)

Maximum enrollment period: From the date of approval to March 31, 2024

Study period: From the date of approval to March 31, 2024

### 8-4. Intervention Methods

During the consumption period of the test food, participants will be instructed to consume 100 mL of the test food at their discretion throughout the day. Each test food will be consumed for four weeks. Participants will be required to keep a record of their intake during the study period. Participants are advised to refrain from strenuous exercise the day before testing and to consume a specified meal by the study conductors by 21:00. After 21:00, participants should arrive at the testing site in a fasting state, except for water, to undergo the testing.

## 8-5. Expected Duration of Participation for Research Subjects

Research participants will participate for a period of 12 weeks after providing consent.

## 9. Examination Items

### 9-1. Examination Schedule

| Examination Items                 | Consent Acquisition      | Eligibility Confirmation | 1st Test Day             | 2nd Test Day             | Test Food Consumption Period |
|-----------------------------------|--------------------------|--------------------------|--------------------------|--------------------------|------------------------------|
| Informed Consent                  |  |                          |                          |                          |                              |
| Background of Participants        |  |                          |                          |                          |                              |
| Consumption of Specified Dinner   |                          |                          |  |                          |                              |
| Restriction of Strenuous Exercise |                          |                          |  |                          |                              |
| Fasting After 21:00               |                          |                          |  |                          |                              |
| Height and Weight                 |  |                          |  |  |      |
| Dietary Intake                    |                          |                          |                          |  |      |
| Thermography                      |                          |                          |                          |  |      |
| Respiratory Gas Analysis          |                          |                          |                          |  |      |
| Visual Analog Scale (VAS)         |                          |                          |                          |  |      |
| Dietary Record                    |                          |                          |                          |                          |      |

